#### Criteria for discontinuing or modifying allocated interventions {11b}

The safety of HP eradication therapy is well known, with the most common adverse events being taste disturbance, diarrhea, nausea, and abdominal pain. The vast majority of adverse events are minor and transient [43]. According to estimates, just 1.3% of patients terminate treatment due to adverse events [44]. Six weeks after ending treatment, all patients will visit the central laboratory of our hospital and undergo stool antigen tests using the enzyme immunoassay method (EIA) [45]. In our research, when individuals report adverse events, the investigators will examine them. The experiment’s drugs may be withdrawn for any of the following reasons: (1) significant adverse events that are considered unsuitable for continuing treatment, such as events that are life-threatening, necessitate inpatient hospitalization, result in persistent or significant disability or incapacity, or may necessitate medical or surgical intervention to prevent one of the outcomes listed above; (2) inability to comply with the trial procedures. Individuals may withdraw from the trial at any time for any reason. The reasons for withdrawal will be noted if individuals indicate them.

#### Strategies to improve adherence to interventions {11c}

Face-to-face treatment and leaflet instruction about the trial will be provided at the initial appointment such as how to take the medication, the potential treatment interactions, side effects, and contraindications; any inquiries will be welcomed either in person by visiting investigators or over the phone. Investigators will discuss the importance of participants completing treatment regimens. Patients are also encouraged to alert investigators if they experience issues linked to trial therapies. Furthermore, participants will be given instructions on how to take trial medications (dosage, timing, and storage), as well as what to do if a dose is missed. Participants will also get a compliance reminder phone call twice a week after treatment begins.

#### Relevant concomitant care permitted or prohibited during the trial {11d}

All other antibiotics, proton-pump inhibitors (PPIs), H_2_ receptor antagonists, non-steroidal anti-inflammatory drugs (NSAIDs), aspirin, herbal remedies, and probiotics will be restricted during the trial procedure.

#### Provisions for post-trial care {30}

As this trial is a low-risk intervention, no particular post-trial care is required. The trial’s risks are covered by insurance at the trial site. It may involve additional health care coverage, reimbursement, or damages.

### Outcomes {12}

The trial’s primary outcome is the percentage of patients who have successfully eradicated HP infection. This will be established based on the findings of stool antigen testing using the enzyme immunoassay method (EIA) [45], 6 weeks after the completion of the first-line treatment phase of the levofloxacin-based concomitant or levofloxacin-based sequential treatment regimen. The HP stool antigen test is an accurate approach for confirming HP eradication after the fourth week following treatment, based on a comprehensive evaluation of 25 reports involving 2078 individuals who examined the HP stool antigen test for confirmation of HP eradication. The sensitivity, specificity, positive predictive value (PPV), and negative predictive value (NPV) were as follows: 88.3%, 92%, 75.1%, and 94.8% [46].

The secondary outcomes are:

The rate of HP eradication of rescue treatments and total eradication rates among the levofloxacin-based concomitant and levofloxacin-based sequential treatment regimens; (2) the type and frequency of adverse events, as well as the rate of compliance, between the levofloxacin-based concomitant and levofloxacin-based sequential treatment regimen groups.

### Participant timeline {13}

Figure 2 summarizes the enrollment, intervention, and assessment timeline.

**Fig. 2 Fig2:**
[figure not shown]
Study schedule of enrollment, intervention, and assessments

### Sample size {14}

We will conduct this as a superiority clinical trial, and the calculation of the sample size is based on the primary outcome, which is the eradication rate of HP infection using ITT. According to a meta-analysis, Kale-Pradhan et al. reported the eradication rate of a sequential levofloxacin-based treatment regimen as 87.8% (P2 = 0.877) [40], while the eradication rate of a concomitant levofloxacin-based regimen was based on the results of a randomized clinical trial conducted in Syria and was 82.05% (P1 = 0.8205) [37]. We applied the following statistical hypotheses: (1) 80% power (*β* = 0.2); (2) the 5% level of significance (*α* = 0.05); and (3) the superiority margin is 10% (*δ* =  − 0.10) and (*ε* = 0.20). Given that *Zα* and *Z*_*β*_ are 1.64 and 0.845, respectively; (4) the ratio of case to control is equal to one (*K* = 1). The sample size formula of the two parallel superiority designs resulted in 64 patients as a sample size for each parallel [47, 48]. We also added 15% for possible dropouts, making the final sample size 150 patients. For more information, please check Additional file 1.

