## Trial design {8}

This is a single-center, prospective, superiority randomized, open-label, active-controlled clinical trial with a 1:1 allocation ratio. Figure 1 shows a trial flow chart.

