## Statistical methods

### Statistical methods for primary and secondary outcomes {20a}

To compare the eradication rate of HP, we will use the ITT analysis (all individuals who got at least one dosage of the trial treatment) and PPA (all individuals who complied and were tested again using a stool antigen test). We will use the *χ*^2^ test, which will be used for nominal variables, such as sex, treatment protocol, treatment outcome based on stool antigen tests, each adverse event, smoking, and alcoholic status, to determine if there is a relationship between the treatment protocol and the result of the treatment for both the primary and secondary outcomes [50]. We will use the *t*-test to compare the means of the continuous variable, such as patient’s age, with the normal distribution for both the primary and secondary outcomes [51]. The difference in eradication rates between the two treatment regimen groups can be assessed by a two-sided 95% confidence interval (CI). Individuals whose stool antigen tests have not been retested including dropouts will be considered treatment failures. The statistical significance level is a *P*-value of 0.05.

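### The 64 patients per arm come from a non-inferiority calculation labelled superiority; the planned superiority test has about 16% power at 150 patients and 27% at 300, not 80%

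*Protocol article*

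**What the plan says.** Trial design {8} describes the study this way: "This is a single-center, prospective, superiority randomized, open-label, active-controlled clinical trial with a 1:1 allocation ratio". Sample size {14} repeats the label: "We will conduct this as a superiority clinical trial".

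The inputs in Sample size {14} are:

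- eradication of 82.05% on concomitant therapy (P1 = 0.8205);
- eradication of 87.8% on sequential therapy, entered as P2 = 0.877;
- 80% power and "the 5% level of significance", with Zα = 1.64 and Zβ = 0.845;
- equal allocation;
- a margin, of which it says "the superiority margin is 10" percent, written as δ = −0.10, together with ε = 0.20.

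The result is: "The sample size formula of the two parallel superiority designs resulted in 64 patients as a sample size for each parallel". After a 15% allowance for dropout the final total is 150. The abstract plans to recruit up to 300, described as double the requirement.

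Statistical methods {20a} plans a chi-square test of the association between regimen and outcome at P = 0.05, and adds: "The difference in eradication rates between the two treatment regimen groups can be assessed by a two-sided 95% confidence interval (CI"). The section mentions no margin, and the protocol nowhere mentions non-inferiority.

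**The concern.** A negative margin in a trial labelled superiority changes the hypothesis. With δ = −0.10 the null hypothesis is that sequential therapy is at least 10 points worse, and the calculation counts the 10 points in favour of the new regimen. The effective distance becomes 15.65 points when the assumed advantage is 5.65. The sample size then supports a hypothesis that the analysis section never tests, while the hypothesis it does test has no valid power statement.

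If so, the primary comparison will most likely be non-significant even when sequential therapy is better by exactly the amount assumed. Such a result could be misread as showing no difference between the regimens. It would also leave room to bring in the −10-point margin after the data are seen. Nothing in the protocol suggests that either is intended, but nothing in it prevents them. The Discussion expects the trial to change first-line treatment in Syria, so the point matters.

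**Working it through.** **Inputs** (Sample size {14}): p1 = 0.8205, p2 = 0.877, Zα = 1.64, Zβ = 0.845, δ = −0.10, 1:1 allocation.

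Variance term: v = 0.8205 × 0.1795 + 0.877 × 0.123 = 0.25515. Assumed difference: 0.877 − 0.8205 = 0.0565.

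**Step 1. Reproduce the stated 64.** The formula is n = (Zα + Zβ)² × v / ((p2 − p1) − δ)².

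- (1.64 + 0.845)² = 6.175, and 6.175 × 0.25515 = 1.5756.
- With δ = −0.10 the denominator is 0.1565² = 0.02449, so n = **64.3**.
- With p2 = 0.878, as in the text, the same formula gives 63.3, which rounds up to 64.

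Either rate leads to the stated figure. The negative sign is needed in both cases.

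**Step 2. Try the other readings** (p2 = 0.877).

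| Reading | n per arm |
|---|---|
| δ = −0.10, one-sided Z = 1.64 | 64.3 |
| δ = −0.10, two-sided Z = 1.96 | 82.0 |
| δ = 0, one-sided Z = 1.64 | 494 |
| δ = 0, two-sided, (1.96 + 0.8416)² = 7.849 | 627 |
| ε = 0.20 as the difference, δ = −0.10 | 17.5 |
| ε = 0.20 as the difference, δ = +0.10 | 158 |
| δ = +0.10 | 833, but meaningless |

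The last row has no meaning because the assumed gain of 5.65 points is below a +10-point margin. The difference being squared is negative, and power to show superiority by 10 points is about 1% at 64 per arm and 0.3% at 150 per arm. The printed ε = 0.20 does not equal the assumed difference and does not lead to 64.

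**Step 3. Power of the planned test.** This is the two-sided 5% chi-square test of zero difference, 82.05% against 87.7%, by exact enumeration of the two binomial distributions. Dropouts count as failures, so treated patients stay in the denominator.

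| Per arm | Total | Two-sided 5% | One-sided 5% |
|---|---|---|---|
| 64 | 128 | 13.8% | 23% |
| 75 | 150 | 16.3% | 26% |
| 150 | 300 | 27.5% | 39% |

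The normal approximation agrees for the two-sided test: 14.2%, 15.9% and 27.6%. Using p2 = 0.878 raises these to 14.6%, 16.4% and 28.4%.

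**Step 4. What the trial can detect.** From a control rate of 82.05%, 80% power with the exact chi-square calculation needs a difference of 13.7 points at 75 per arm and 10.6 points at 150 per arm. Normal approximations give about 14 and 10.6–10.7. The 95% confidence interval half-width at 150 per arm is 1.96 × √(0.25515/150) = 8.1 points, wider than the assumed effect of 5.65.

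**Step 5. Read as non-inferiority at −10 points** (normal approximation, same rates). At 64 per arm, power is 80% with a one-sided 5% test, which matches the protocol's claim, but 70% if the planned two-sided 95% interval is the criterion. With that interval it is 77% at 75 per arm and 97% at 150 per arm.

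**The case against.** The strongest reply is that the fault lies in the label and the trial is not too small. The planned two-sided 95% interval could be compared with −10 points, and at 150 per arm that comparison has 97% power. The arithmetic itself is also sound for the inputs printed. Both statements are true. However, the protocol calls itself a superiority trial in the abstract, the design section and the sample size section, and its named test is a chi-square test without a margin. Nowhere does it commit to judging the interval against −10 points. The power of the test it does commit to is the power in Step 3.

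A second reply is that the formula and the meaning of ε may be explained in Additional file 1 or the cited sources, which are not shown here. That could explain what ε stands for. It would not change the conclusion, because the printed inputs reproduce 64 without it and the negative sign is printed in the text.

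A third reply is that recruiting up to 300 gives ample reserve. It doubles a requirement that was calculated for a different hypothesis, and it is a ceiling. At 300, superiority power is still only 27%.

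**Conclusion.** The concern holds. The figure of 64 per arm is a one-sided 5% non-inferiority sample size with a −10-point margin, presented as a superiority sample size. For the planned superiority test, the stated 80% power is in fact about 16% at 150 patients in total and about 27% at 300. Under the protocol's own assumptions, a non-significant primary result is therefore expected roughly 73% to 84% of the time. The most favourable superiority reading, a one-sided 5% test, reaches only 39% at 300 patients.

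This rests on the protocol's own eradication rates and on the chi-square test at P = 0.05 as planned. Choosing 87.7% or 87.8% for sequential therapy moves power by about one percentage point or less. The abstract can be read as 150 in total or 150 per arm, and the two figures cover both readings. This must be corrected.

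**What to change.** Rewrite Sample size {14} and Additional file 1 so that hypothesis, formula and test agree, and carry the change into Trial design {8} and Statistical methods {20a} where needed. There are two coherent routes.

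**(a) Keep superiority.** Delete the 10% margin and ε = 0.20, and use a two-sided 5% level. State that 150 per arm gives about 27% power for a 5.65-point difference and 80% power for about 10.6 points. The text should acknowledge that 82.05 + 10.6 = 92.65%, which is above any first-line rate the protocol cites.

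**(b) Declare what was calculated.** Make the primary hypothesis non-inferiority of sequential to concomitant therapy at −10 points, judged by the lower limit of the two-sided 95% interval for the difference. Test superiority at zero next, in fixed sequence. State about 97% power for the first step at 150 per arm and about 27% for the second. The sponsor must justify the margin clinically, since the protocol gives no basis for 10 points.

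Under either route, say whether the planned size is 150 or 300 in total and quote power for that number.

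The cost is wording and a corrected supplementary file, with no extra patients. The price is a less favourable power statement under (a) or a changed primary objective under (b). Enlarging the trial to full superiority power looks out of reach. It needs about 2 × 627 = 1,254 patients, while 10 to 15 new diagnoses a month over the 35 months from October 2023 to August 2026 yields about 350 to 525. Trial status reports no patients enrolled at protocol version V3, so the change belongs before any outcome is compared by arm.

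### The 150-patient calculation falls short of 80% power for the planned two-sided ITT analysis, even if the −10-point margin is accepted; a full 300 would meet it against that margin

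*Protocol article*

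**What the plan says.** The protocol article's Sample size {14} section bases the calculation on the eradication rate under ITT. It sets 80% power and "the 5% level of significance", and says that Zα and Zβ "are 1.64 and 0.845, respectively". The concomitant rate "was 82.05% (P1 = 0.8205"; the sequential rate is entered as P2 = 0.877. On the margin it says "the superiority margin is 10" per cent, with δ = −0.10. The result is 64 per arm, and then: "We also added 15% for possible dropouts, making the final sample size 150 patients". The Abstract (Method) plans up to 300 patients and describes that as double the requirement.

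The analysis is set out in Statistical methods for primary and secondary outcomes {20a}. It uses a chi-square test, and "The difference in eradication rates between the two treatment regimen groups can be assessed by a two-sided 95% confidence interval (CI"). It adds: "The statistical significance level is a *P*-value of 0.05". The ITT set is everyone who took at least one dose. On losses it says: "Individuals whose stool antigen tests have not been retested including dropouts will be considered treatment failures".

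**The concern.** Two steps in the calculation do not match the analysis.

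- **Sidedness.** Zα = 1.64 belongs to a one-sided 5% test. A two-sided 95% interval uses 1.96, and the protocol plans no one-sided test.
- **Dropouts.** Adding 15% restores the intended number of evaluable patients when dropouts leave the analysis. Here treated dropouts stay in the denominator as failures. They lower both rates and shrink the difference between them, and extra patients do not bring back 82.05% and 87.7%.

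The practical risk is that 150 is called the final sample size and 300 is only an upper limit. A team that stopped near 150 would believe it had 80% power, and would believe that 300 gave a twofold surplus.

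**Working it through.** **Inputs** (Sample size {14}): P1 = 0.8205, P2 = 0.877, difference 0.0565, δ = −0.10, Zα = 1.64, Zβ = 0.845, 1:1 allocation. Variance term V = 0.8205 × 0.1795 + 0.877 × 0.123 = 0.14728 + 0.10787 = 0.25515.

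**1. Reproducing the plan's figure.**
n = (Zα + Zβ)² × V / ((P2 − P1) − δ)² = 2.485² × 0.25515 / 0.1565² = 64.3 per arm. This matches the stated 64. For the total, 128 × 1.15 = 147.2 and 128 / 0.85 = 150.6, so 150 is consistent with a 15% allowance. (The printed ε = 0.20 would give 17.5 per arm, so it was not the value used; that is a separate matter.)

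**2. Same margin, planned two-sided interval.**
Required n = (1.96 + 0.845)² × 0.25515 / 0.1565² = 7.868 × 0.25515 / 0.02449 = 82 per arm, 164 in total.
Power = Φ(0.1565 / √(V/n) − z):

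- 64 per arm: 0.1565 / 0.06314 = 2.479. With z = 1.645, 79.8%; with z = 1.96, 69.8%.
- 75 per arm: 0.1565 / 0.05833 = 2.683. With z = 1.645, 85.0%; with z = 1.96, 76.5%.
- 150 per arm: 0.1565 / 0.04124 = 3.795. With z = 1.96, 96.7%.

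The 150-patient size therefore misses 80% on sidedness alone, even if all 75 per arm count at the assumed rates. Also, 300 / 164 = 1.8, not 2.

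**3. Treated dropouts counted as failures.** This step assumes that the source rates exclude losses and that a fraction d is lost equally in both arms. Both rates are then multiplied by (1 − d). At d = 0.15 the rates are 0.697 and 0.745, the difference is 0.048 and V = 0.4008. Required n = 7.868 × 0.4008 / 0.148² = 144 per arm.

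| Loss d | ITT rates | Needed per arm (total), two-sided | Power at 75 per arm, one-sided | Power at 75 per arm, two-sided | Power at 150 per arm, two-sided |
|---|---|---|---|---|---|
| 0% | 82.05% / 87.7% | 82 (164) | 85.0% | 76.5% | 96.7% |
| 5% | 77.9% / 83.3% | 104 (208) | 77.1% | 66.5% | 92.2% |
| 10% | 73.8% / 78.9% | about 124 (248) | 70.3% | 58.7% | 86.9% |
| 15% | 69.7% / 74.5% | 144 (288) | 64.8% | 52.6% | 81.7% |

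A simulation of the two-sided interval (400,000 trials per setting) agrees: 77.2% and 52.6% at 75 per arm with 0% and 15% loss, and 96.7% and 81.7% at 150 per arm.

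**4. The test of zero difference.** The chi-square test in {20a} addresses no difference, not −10 points. Power = Φ((0.0565 − 1.96 × SE₀) / SE₁), with SE₀ from the pooled rate 0.84875 and SE₁ = √(V/n):

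- 75 per arm: (0.0565 − 1.96 × 0.05851) / 0.05833 = −1.00, so about 16%.
- 150 per arm: (0.0565 − 1.96 × 0.04137) / 0.04124 = −0.60, so about 28%.

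Both are undiluted; losses counted as failures lower them.

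**The case against.** A reader might infer that the trial as planned cannot reach 80% power, or that 300 is merely the required number. The documents do not support either as a general statement. Against −10 points, 150 per arm gives 96.7%, and still 81.7% with both corrections and the full 15% lost. The requirement approaches 300 (288) only in that last case.

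The dropout part is also conditional. The protocol does not say whether 82.05% and 87.8% are ITT rates, and the sources and Additional file 1 are not at hand. If losses are already inside those rates, no dilution applies and the shortfall at 150 is 3.5 points. The 15% is an allowance rather than a forecast, and patients lost before any dose leave the ITT set, so it is an upper case.

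These points stand, and they limit the finding to the 150-patient figure. They do not remove it. The sidedness mismatch needs no assumption about dropouts. And 300 is a ceiling: Recruitment {15} gives 10 to 15 new diagnoses a month, and October 2023 to August 2026 (Trial status) is about 34 months. That yields 340 to 510 patients before exclusions and refusals, so reaching 300 needs roughly 59% to 88% of them.

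A further fair objection is that {20a} does not tie the interval to −10 points, so the margin-based power is not clearly the power of the stated analysis. That also stands, and it shapes the fix.

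**Conclusion.** The stated 80% power does not hold for the 150-patient size under the planned two-sided analysis, even with the −10-point margin taken as given. On sidedness alone, power is 76.5% at 75 per arm and 164 patients are needed. The 15% add-on is inconsistent with failure-counting ITT in one of two ways:

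- If the source rates exclude losses, power at 150 is between 67% and 53% for losses of 5% to 15%.
- If the source rates already include losses, the add-on is not needed and 76.5% applies.

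The trial itself is affected only if recruitment ends well short of 300. The figures rest on the protocol's own rates, the unpooled normal approximation and, for the diluted cases, equal loss in both arms. Whether a −10-point margin suits a superiority trial is a separate and larger question that this point leaves open.

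**What to change.** In Sample size {14}:

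- Recalculate with Zα = 1.96.
- State whether each source rate counts losses as failures. Use ITT rates accordingly, in place of a separate 15% inflation.
- Report power at both 150 and 300, and label it as power against the −10-point margin only.
- Beside it, give the power of the planned two-sided test of zero difference: about 16% at 150 and 28% at 300 under the same rates, lower with losses. Quoting the margin-based figure alone would reassure falsely.

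In the Abstract, correct the statement that 300 is double the requirement: it is about 1.8 times 164 undiluted, and barely above 288 with 15% loss.

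The cost is wording and a less favourable stated power. No patients beyond the 300 already foreseen are needed to reach 80% against the −10-point margin.

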### Recruitment {15}

Participants will be recruited through Damascus Hospital’s outpatient clinic. We also have a dedicated phone line to answer any questions about participating in the study. On average, our outpatient clinic sees 10 to 15 newly diagnosed HP-infected patients per month. The investigators will explain the trial to eligible patients and ensure they understand the hazards of participating. Before taking part in the experiment, patients will need to sign an informed consent form.

## Assignment of interventions: allocation

### Sequence generation {16a}

An independent assistant will generate a randomized number table using LibreOffice Calc’s RANDBETWEEN function [49].

### Concealment mechanism {16b}

The independent assistant will keep the randomized number table sealed in an envelope.

### Implementation {16c}

Once a researcher has obtained the patient’s informed consent, they will contact the independent assistant to get the allocated treatment regimen.

## Assignment of interventions: blinding

### Who will be blinded {17a}

It is challenging to blind the participants and the researchers in this open-label trial. However, throughout the whole trial, laboratory medical professionals, data collectors, and data analysts will remain blinded to the therapy allocation. The allocation information will be hidden on a data collection form for adverse events and compliance, and data collectors are not permitted to inquire about participants' regimens.

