### Interventions

#### Explanation for the choice of comparators {6b}

For two weeks, patients on the concomitant levofloxacin regimen will receive levofloxacin 500 mg once daily, amoxicillin 1000 mg, tinidazole 500 mg, and esomeprazole 20 mg twice daily. When applied as a first-line treatment, the previous regimen had the highest eradication rate for Syrian patients naive to HP treatment [36, 37]. A rescue regimen of high-dose dual therapy consisting of esomeprazole (40 mg twice daily) and amoxicillin (1000 mg three times daily) for 2 weeks will be used after first-line treatment fails [22, 39].

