#### Intervention description {11a}

The sequential levofloxacin regimen consists of esomeprazole 20 mg and amoxicillin 1000 mg taken twice daily for 1 week, followed by metronidazole 500 mg, esomeprazole 20 mg twice daily, and levofloxacin 500 mg once daily for 1 week [22, 40]. Microscopic examination of the stomach biopsies and hematoxylin and eosin, followed by Giemsa stains [41], will be used to confirm HP infection, which has a sensitivity and a specificity of 95% and 99%, respectively [41]. Gastric biopsies will be collected via gastroduodenoscopy and forwarded to the pathology laboratory of the same referral hospital. According to the Sydney system [42], endoscopists obtained five stomach biopsies: two from the body, two from the antrum, and one from the incisura. If the first-line treatment fails, a high-dose dual therapy of PPI and amoxicillin will be provided as a rescue therapy [22].

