## Data collection and management

### Plans for assessment and collection of outcomes {18a}

During screening, sociodemographic and baseline information (including age, sex, contact information, and past medical history) will be obtained. The success of HP eradication will be assessed by stool antigen assays performed with the enzyme immunoassay method (EIA) 6 weeks following the completion of therapy [45]. Participants will be prohibited from using PPIs, antibiotics, H_2_ receptor antagonists, aspirin, herbal remedies, and probiotics for 8 weeks until the stool antigen testing. The stool antigen tests must be performed no later than 6 weeks + 3 days after the completion of therapy. The data on adverse events and compliance will be obtained face-to-face and documented using the data collection form no later than 3 days following the completion of therapy. The count of pills taken will be used to determine study drug compliance. The data will be obtained from two trained assistants who are instructed to collect the information in a consistent, reproducible manner, and the integrity of the data will be overseen by the principal investigator.

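### Data collectors are declared blinded throughout, but the pill count that the protocol assigns to compliance is not covered by the two stated safeguards, which exposes mainly the adverse-event comparison

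*Protocol article*

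**What the plan says.** Protocol article, Who will be blinded {17a}: the trial is open-label, and the section concedes that "It is challenging to blind the participants and the researchers in this open-label trial". It nevertheless states that "throughout the whole trial, laboratory medical professionals, data collectors, and data analysts will remain blinded to the therapy allocation". The means are given in the next sentence: "The allocation information will be hidden on a data collection form for adverse events and compliance, and data collectors are not permitted to inquire about" the participants' regimens.

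Protocol article, Plans for assessment and collection of outcomes {18a}: "The data on adverse events and compliance will be obtained face-to-face and documented using the data collection form", within 3 days of the end of therapy. On compliance: "The count of pills taken will be used to determine study drug compliance". On who does this: "The data will be obtained from two trained assistants". The word 'from' is read here as 'by', since the sentence goes on to say how the assistants are instructed to collect.

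The regimens:
- Concomitant, for two weeks (Explanation for the choice of comparators {6b}): "levofloxacin 500 mg once daily, amoxicillin 1000 mg, tinidazole 500 mg, and esomeprazole 20 mg twice daily".
- Sequential (Intervention description {11a}): "esomeprazole 20 mg and amoxicillin 1000 mg taken twice daily for 1 week, followed by metronidazole 500 mg", with esomeprazole continued and levofloxacin once daily in the second week.

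Three other places matter:
- Outcomes {12} makes adverse events and compliance between-group secondary outcomes.
- Statistical methods {20a} makes compliance a condition for the per-protocol analysis.
- The Discussion defines compliance as taking more than 80% of what was prescribed. It also voices concern about compliance because drugs change between the first and second week.

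**The concern.** The two safeguards deal with what is printed on the form and what the collector may ask. Neither deals with what a pill count shows. If the assistant who records adverse events also counts the pills, the drug names and numbers disclose the arm.

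This matters because most of the events that the protocol names as common (nausea, abdominal pain, altered taste, diarrhea) are largely symptoms whose recording depends on how they are asked about and graded. Participants are already unblinded, so a blinded collector is the protection against differential probing that the plan claims for this outcome. The protocol also states in advance a worry that applies to the sequential arm only, so an assessor who knows the arm has an expectation to act on. A trial report that repeated the blinding statement as it stands would claim a property that the described procedure does not deliver for the pill counter.

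**Working it through.** The protocol gives no figure to reproduce. The check is whether a pill count can be made and classified without the allocation.

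**Inputs.** Regimens from {6b} and {11a}; the 80% rule from the Discussion. 'Twice daily' is read as applying to amoxicillin, the nitroimidazole and esomeprazole alike.

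**Step 1: prescribed doses by drug** (doses per day × days)

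| Drug | Concomitant | Sequential |
|---|---|---|
| Levofloxacin | 1 × 14 = 14 | 1 × 7 = 7 |
| Amoxicillin | 2 × 14 = 28 | 2 × 7 = 14 |
| Tinidazole | 2 × 14 = 28 | none |
| Metronidazole | none | 2 × 7 = 14 |
| Esomeprazole | 2 × 14 = 28 | 2 × 14 = 28 |

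Only esomeprazole has the same count in both arms. A count recorded by drug shows the arm from the nitroimidazole alone.

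**Step 2: could a single total hide the arm?** Tablet strength is not given, so let *a* be the number of units per 1000 mg amoxicillin dose (assumed 1, 2 or 4), with one unit per dose of every other drug.

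- Concomitant total = 14 × (1 + 2a + 2 + 2)
- Sequential total = 7 × (2 + 2a) + 7 × (2 + 2 + 1)

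| a | Concomitant | Sequential | Sequential ÷ concomitant | 80% of concomitant |
|---|---|---|---|---|
| 1 | 98 | 63 | 64.3% | 78.4 |
| 2 | 126 | 77 | 61.1% | 100.8 |
| 4 | 182 | 105 | 57.7% | 145.6 |

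In every row, 80% of the concomitant course exceeds the entire sequential course.

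**Step 3: classification.** Take a = 1 and 63 units taken. In the sequential arm this is 63/63 = 100%, compliant. In the concomitant arm it is 63/98 = 64.3%, not compliant. The same count has opposite meanings, so whoever turns it into a percentage must know the arm. A total alone does not always identify the arm, since a poorly adherent concomitant patient can match a fully adherent sequential one. A total above the full sequential course, however, can only come from the concomitant arm.

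**Step 4: who does this?** {17a} puts adverse events and compliance on the form that the data collectors complete. {18a} has both obtained face-to-face, names two assistants, and bases compliance on the pill count. Read together, the natural meaning is that the same assistants do both tasks.

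**Step 5: which outcomes are reached?**
- Adverse events: yes, through what is asked and how it is classified.
- Per-protocol membership: only slightly, because a count is numeric and leaves an assessor little discretion.
- Intention-to-treat eradication: no. It rests on a laboratory stool-antigen immunoassay, with laboratory staff stated to be blinded and untested patients counted as failures.

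**The case against.** The case against is that much of this is inferred. The article does not describe packs, tablet appearance or pack return. It puts the pill count in the passive and does not say who counts or who converts the count to a percentage. The section on the coordinating center {5d} gives a data manager charge of data collection, so the division of tasks is not fully fixed. A collector could write down a count and someone holding the allocation could convert it later. Other controls exist: uniform collection instructions, double-checking of entries and an independent audit.

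Most of this stands as a limit on the point. A reader might infer that the assistants handle visibly different packs, that blinding is impossible, or that collector blinding is the only protection in the trial. The documents do not support these: appearance and handling are not described, a separate counter could preserve blinding, and the other controls are real, although none of them blinds anyone. A reader might also infer that the main efficacy result is biased. It is not reached, as step 5 shows.

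Later conversion by someone else does not remove the problem. It moves the denominator away from the collector, but a count by drug still shows the arm to the person who makes it.

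It can also be said that the order of tasks at a visit is detail that an article leaves to the full protocol. That would answer a complaint of silence. Here the article makes a positive claim of blinding and describes a procedure that does not support it. Finally, unblinded patients report their own symptoms, and that source of bias remains whatever is done about the collectors.

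**Conclusion.** The point holds in a limited form. The protocol claims blinding for all data collectors throughout, and the two safeguards that it gives do not keep the pill counter blinded. On the natural reading, the pill counter is also one of the two assistants who record adverse events.

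The exposure covers the adverse-event comparison first and per-protocol membership to a smaller degree. The primary intention-to-treat comparison is unaffected. The dose counts show that the regimens can be told apart; they do not show that any outcome will be biased, and no size of bias can be derived.

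The conclusion assumes that the assistants named in {18a} are the data collectors of {17a} and that they make the count. If the full protocol gives the count to a separate person, what remains is a clarification of wording. It should be corrected before data are collected, because the change is small and the claim will otherwise be carried into the report.

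**What to change.** At the end-of-treatment visit, split the two tasks and fix their order.

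1. One assistant completes and closes the adverse-event form first, without seeing the drugs. The form uses a standard open question plus a checklist that includes, but is not limited to, the events named in {11b}. A checklist restricted to those would narrow capture, since {22} tracks any event arising or worsening after the first dose.
2. The other assistant then counts the pills and is declared unblinded. As {19} also has two assistants entering and double-checking data, this person should not enter or check adverse-event records before that form is locked.
3. Analysts receive compliance only as a percentage and as yes/no at the 80% rule, not as counts by drug.
4. Reword {17a} to claim blinding for the adverse-event collector, laboratory staff and analysts, and not for pill counting. State that unblinded patients may still reveal their regimen.

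The cost is a set task order and a few sentences in {17a} and {18a}. It needs no new staff if the two existing assistants can both attend, and that attendance is the main downside. Treatment and the primary analysis do not change.
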